**Physical therapist**	
**Inclusion**	
- At least 2 years’ experience of treatment with training for musculoskeletal disorders	
- Treat patients with a knee injury on a weekly basis	

Clinics, as opposed to participants, are randomized in order to avoid familiarization with both conditions within the same clinic or the individual PT, a potential source of contamination which could influence intervention adherence and therefore skew results. In accordance with the Swedish health care system, participants select their clinic, and clinics do not actively advertise in order to recruit patients (making randomization at the participant level impossible), so self-selection of a treatment arm is theoretically random and blinded. PTs are given information on the methodology of their assigned intervention arm to allow them to recruit participants from their population.

Due to the nature of the design, as well as practical constraints (i.e., necessity of familiarity with intervention, staff availability), neither the study coordinator (SC), participants, nor PTs can be blinded. As a result, the test leader is blinded to the treatment condition and un-blinding is not permissible. Final data analysis is performed by a blinded third party in order to avoid potential bias.

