#### Main outcomes

This trial includes two main outcomes. Psychological readiness to return to sport is evaluated using the Swedish version of the ACL-Return to Sport after Injury scale (ACL-RSI), which includes an emotional response, confidence, and risk-appraisal when returning to sport after an ACL injury [33, 34]. Physical function is evaluated using the change in number of hops in the injured leg from baseline to 12 weeks for the side hop task.

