### Statistical analyses

#### Sample size

Based on previous studies examining ACL-RSI [49] and side-hop function [50], a preliminary sample size was estimated, to be used in the first phase of this adaptive RCT, which resulted in *n*=106 participants. This included adjustments for potential cluster effects using a preliminary Intra-Cluster Correlation Coefficient (ICC). An approximation is required as comparable studies are unavailable to reliably perform a sample size estimation. This is necessary in this phase in order to evaluate whether an intervention effect is detectable and within practical limitations, which will thereafter inform more accurate sample-size estimations.

A new sample size will be calculated by a blinded third-party member of the data management committee using collected data from an interim analysis, therefore allowing for more accurate between-group differences in the main outcomes. Observed within- and between-cluster variance will also be calculated in order to more accurately estimate an Intra-Cluster Correlation Coefficient (ICC, denoted as *ρ*). This will be performed using the formula $$ \rho =\frac{s_b^2}{s_b^2+{s}_w^2} $$ [51] in order to adjust for the fact that different clinics are included in the trial (i.e., potential clustering effects). The adjusted sample size will therefore be calculated using the formula $$ \frac{n_ik\left(1-\rho \right)}{k-{n}_i\rho } $$ [52], along with an estimated 20% drop-out rate, in order to reach a power of 0.80, with significance set at *p*<0.025. As an estimated sample size has been calculated, the new sample size will only be adjusted up; that is, the number of participants included will not be less than *n*=106 required in the original sample-size estimation.

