#### Data analysis

The analysis will be done using the IBM SPSS statistical software package (IBM Corp., Armonk, New York, USA). Primary analyses of the entire sample will be done according to intention-to-treat principles. A dose-response analysis will be performed to determine effective adherence. Per-protocol analyses will be performed for those participants with at least 70% adherence (corresponding to two trainings per week), as a preliminary estimate of the effective number of training occasions. This is in order to eliminate cross-over and drop-out effects in the total sample, as well as to evaluate the training for those that have reached a pre-defined level of adherence deemed acceptable to have an effect. Sensitivity analyses will be performed to determine whether within-cluster correlations indicate potential effects due to being clustered, for example, by the clinic or by PT. Patient cross-over (i.e., patients changing clinics) is a low-risk possibility and will be recorded in case of occurrence. All outcome variables will be examined for normality using appropriate testing (e.g., Kolmogorov-Smirnov). Complete-case analyses are the primary analyses, and sensitivity analyses will be done depending on the number of missing values. Missing values are not expected to be extensive, and if less than 5% of data is missing, the whole data set will be analyzed along with a sensitivity analysis with appropriate imputed values. If between 5 and 40% of data is missing, appropriate multiple imputation methods will be used, which will be informed by blindly assessing results of the interim analysis, and a complete-case analysis will be done with appropriate sensitivity analyses. If over 40% is missing, a complete case analysis will be done with no sensitivity analysis.

Results will be analyzed using independent samples *t* tests to examine between-group differences of the change from baseline to a 12-week follow-up. Where appropriate, equivalent non-parametric Wilcoxon signed-rank testing will be used to compare between-group differences. The main analysis will focus on the two main outcomes, with secondary outcomes acting as support for these. Secondary outcomes therefore carry less weight and issues with potential error due to the number of evaluations will be discussed when results are presented.

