Limitations include that only the test leader is blinded to condition assignment due to the nature of the design. As the study coordinator is not blinded, bias cannot be ruled out during recruitment. Information to participants includes a brief description of the aims of the study in line with Swedish ethical guidelines, which may influence participants’ decision to participate or their behavior during the trial (i.e., if aware of a mental training intervention, more focus may be placed on mental aspects). However, as the participants receive no specific information, and imagery is assessed as a compliance measure, this is not seen as problematic. A further limitation includes that previous studies do not provide relevant data for sample size calculation. Mean differences, standard deviations, and variance are therefore theoretical, leading the authors to use an adaptive design in order to collect data which may be used for sample-size re-calculation. Simulation analyses, which may provide more accurate estimations, were not used to estimate sample size as these theoretical and estimated values would not provide reliable results. This highlights the adaptive nature of this trial and having collected data will provide information necessary to perform reliable sample size and power calculations for future research. This trial presents challenges in that it introduces the more holistic MOTIFS model, which shifts the clinical paradigm and places more focus on the individual and their context-specific needs from a psychological perspective. In order to aid in this, individual visits with the SC, as well as guidance and workshops, will smooth the transition to the novel MOTIFS training model.

Along with publication in a peer-reviewed journal, results of the study will be communicated via a popular science article in order to inform potential end-users of the outcome of this trial, with the aim of making the MOTIFS model readily available for use by end-users.

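### Both main outcomes are tested as unadjusted change scores, although adjusting for the baseline values already collected would generally be more precise

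*Protocol article*

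**What the plan says.** The Data analysis section of the Protocol article compares the arms with independent-samples t tests "to examine between-group differences of the change from baseline to a 12-week follow-up", with a rank-based alternative where appropriate. It names no covariate for this comparison. The sensitivity analyses it lists concern clustering and missing values, so baseline adjustment does not appear there either.

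The Main outcomes section opens: "This trial includes two main outcomes. Psychological readiness to return to sport is evaluated using the Swedish version" of the ACL-RSI. Of the second outcome it says: "Physical function is evaluated using the change in number of hops in the injured leg from baseline to 12 weeks for the side hop task". Under Outcome assessment, patient-reported and physical outcomes are collected at baseline and at 12 weeks, so both baseline values will be available.

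The Sample size section gives a preliminary total of 106. The recalculation after the interim analysis is to be made "along with an estimated 20% drop-out rate" and "in order to reach a power of 0.80", at a significance level of 0.025.

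**The concern.** A change score fixes the weight of the baseline value at exactly 1. ANCOVA estimates that weight from the data. Unless the true slope of the 12-week value on baseline is close to 1, the fixed weight leaves avoidable noise in the comparison.

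The Discussion admits that the planning values are theoretical, and the section on modification criteria treats more than 100 patients per group as unrealistic. Such a trial has reason to use the precision it can get from data it already collects.

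There is a second, smaller matter. If the arms happen to differ at baseline by chance, part of that gap is expected to close by 12 weeks without any treatment effect. An unadjusted change score counts the closing as benefit to the arm that started worse. The article fixes this method itself, so the choice is not simply left to a separate analysis plan.

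**Working it through.** **The plan's own figure.** The total of 106 cannot be reproduced, because the article gives neither the difference, the SD nor the intra-cluster correlation behind it. Working backwards with two-sided alpha 0.025 (sidedness is not stated, so this is an assumption), power 0.80 and no clustering:

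- 53 per arm: d = (2.241 + 0.842) × √(2/53) = 0.60
- 42.4 per arm after 20% drop-out: d = 3.083 × √(2/42.4) = 0.67

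The comparison below is therefore relative.

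**Inputs.** From the article: two arms at 1:1, 106 participants, 20% drop-out, alpha 0.025, power 0.80. Assumed, because the article does not give them: r from 0.3 to 0.9, equal SD s at both visits, independent patients.

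**Precision.**

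- Variance of a change score: 2(1−r)s²
- Residual variance under ANCOVA: (1−r²)s²
- Ratio: (1−r²) / [2(1−r)] = (1+r)/2

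If the change-score test has exactly 80% power, ANCOVA has power Φ(3.083/√((1+r)/2) − 2.241).

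| r | variance ratio | variance saved | patients matching 106 | power of ANCOVA |
|---|---|---|---|---|
| 0.3 | 0.65 | 35% | 69 | 94% |
| 0.5 | 0.75 | 25% | 80 | 91% |
| 0.7 | 0.85 | 15% | 91 | 87% |
| 0.9 | 0.95 | 5% | 101 | 82% |

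A simulation with 42 per arm, 4000 runs, no clustering and no treatment effect agrees. At r = 0.3, 0.5 and 0.7 the SDs of the estimates were 0.254, 0.218 and 0.166 for the change score and 0.208, 0.191 and 0.153 for ANCOVA. The squared ratios are 0.67, 0.77 and 0.85.

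**Unequal SDs.** Let k be the SD at 12 weeks divided by the SD at baseline, and β = rk the slope. In units of the baseline variance, the change-score variance is 1 + k² − 2rk and the ANCOVA variance is k²(1−r²). The difference is (1−β)². The gain is therefore zero at β = 1, for example r = 0.7 with k = 1.43, where β = 1.00.

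**Chance imbalance.** Given a chance baseline gap b, the expected change-score difference moves by (1−β)b, which is (1−r)b with equal SDs, towards the arm that starts worse. For an assumed b = 0.3 SD:

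| r | shift (SD) | effect detectable with 80% power at 42 per arm (SD) | shift as share of that effect |
|---|---|---|---|
| 0.3 | 0.21 | 0.80 | 26% |
| 0.5 | 0.15 | 0.67 | 22% |
| 0.7 | 0.09 | 0.52 | 17% |
| 0.9 | 0.03 | 0.30 | 10% |

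The SE of the baseline difference with 53 per arm is √(2/53) = 0.19 SD, so a chance gap above 0.3 SD in either direction has a probability of about 12%. With an assumed design effect of 2 it is about 27%.

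Averaged over repeated randomisation the shift cancels. With no imbalance built in, the simulated rejection rate of the change-score test was 0.023 to 0.025 against a nominal 0.025.

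**The case against.** A prespecified comparison of change is a recognised method and is unbiased over repeated randomisation. The article also defines the side-hop outcome as a change. Both points stand, which makes this a question of efficiency rather than of a wrong test.

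The size is assumed throughout. The article gives no correlation, no SDs and no imbalance. The saving is only 5% at r = 0.9 and nil at a slope of 1. The figures treat patients as independent although clinics are randomised, and the patient-level correlation need not govern the variance between clinics. This stands too, and is why a range is shown.

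A reader might go further. The section on participants and randomization says that "self-selection of a treatment arm is theoretically random and blinded", while the Discussion concedes: "As the study coordinator is not blinded, bias cannot be ruled out during recruitment". From this one could infer that recruitment after allocation will make the arms differ at baseline, that the change score will turn the difference into a false effect, and that ANCOVA would cure it. The documents do not support that chain:

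- Entry rests on rehabilitation stage and hop ability. Baseline physical testing follows confirmation of hop ability and is done by a test leader blinded to arm. Nothing says that recruiters see the baseline scores beforehand.
- Under Procedure, knee injuries are reported weekly, the coordinator tries to approach every potential participant, and the numbers eligible, ineligible and declining are recorded.
- If recruitment nevertheless produced stable differences, an arm starting lower by b would stay lower by b. The expected difference in change would then be zero, and ANCOVA would be off by (1−r)b against that arm: the same 0.15 SD at b = 0.3 SD and r = 0.5, in the opposite direction.

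Whether patients' choice of clinic can be called random is a recruitment question that no covariate settles.

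**Conclusion.** The point holds as a recommendation on efficiency. The stated primary comparison leaves out a baseline value that is already collected. With equal SDs and independent patients this costs between 5% and 35% of the variance over r = 0.9 to 0.3, and nothing if the slope is near 1. A chance baseline gap also shifts the unadjusted result by (1−r)b, conditional on the gap that occurs. None of this shows that the planned test is biased on average or that its type I error is wrong, and it does not address selection after allocation.

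**What to change.** In the Data analysis section, make the primary analysis of each main outcome a regression (ANCOVA) with treatment arm and the baseline value of the same outcome as covariate. Report the adjusted difference with its confidence interval.

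Side hop may stay defined as change: regressing change, or the 12-week value, on arm and baseline gives the same treatment estimate, and only the baseline coefficient differs, by 1. Keep the unadjusted comparison of change as a sensitivity analysis. The baseline term should sit in whatever model is used to account for clinic. The article's main test is a plain t test, so how clinic enters is a separate decision. This point needs no further covariates.

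The cost is one degree of freedom per outcome and a change of wording, made before any unblinded analysis. No additional data are needed.

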### Participants and randomization

Approximately 106 participants are recruited according to inclusion criteria (Table 1) from physical therapy clinics in Sweden. Physical therapists (PTs) fulfilling inclusion criteria (Table 1) from these clinics are included in the trial. The eligibility criteria for both PTs and participants allow for the recruitment of a sample of knee-injured people and their PTs representative of the population. To avoid contamination, participating clinics are block randomized by a third party using a random numbers generator and sealed opaque envelopes to either the experimental or CaU condition.

**Table 1 Tab1:** Participant and physical therapist inclusion and exclusion criteria

Participants	
Inclusion	Exclusion
- Men and women 16 years or older - Traumatic knee injury (e.g., ligament, meniscal, patellar, or chondral injury), with or without surgical intervention, and involving one or more knee structures - Currently undergoing physical therapist-supervised rehabilitation training - Have reached the stage in their rehabilitation which includes single-leg hop training, as well as a change of direction - Active before the injury in recreational or competitive physical activity, with a goal of returning to physical activity	- Any degenerative knee disorder (e.g., osteoarthritis), or other disease or disorder (e.g., spine disorder, neurological disease) overriding the traumatic knee injury - Reached end-stage rehabilitation (i.e., have undergone a return to physical activity evaluation by their physical therapist, or is estimated to return less than 12 weeks from potential inclusion date) - Do not understand the languages of interest (Scandinavian languages, English)

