#### Outcome assessment

Physical and patient-reported outcomes are assessed at baseline and 12 weeks; patient-reported outcomes are assessed 12 months post-inclusion (Fig. 1). Prior to the testing occasion, self-report questionnaires are distributed using the REDCap electronic data capture tool [32], hosted by Lund University. Demographic data (age, gender, height, weight, treatment type, and injury history) and physical testing data (Table 3) are collected by an experienced test-leader either at the participants’ respective clinics or at the university lab according to a data collection form including testing procedures (further information is available in the data management plan, available at the ClinicalTrials.gov registration page: NCT03473821). Outcomes are assessed at 12 weeks post-inclusion to assess physical and psychological readiness when a PT would likely consider a return to activity testing, and at 12 months to assess long-term rehabilitation outcomes.

**Table 3 Tab3:** Outcomes assessment—description of types of outcome and the data used for analysis

Outcome		Type	Outcome data
Patient-reported outcomes	ACL-RSI^a^	12 item self-report scale (0–100 for each item)	0% (worst) to 100% (best) mean of summed total score
	KOOS	The normalized score for subscales: pain, symptoms, sports and recreational activity, activities of daily life, and quality of life	0 (worst) to 100 (best)
	PACES	18-item self-report scale (11 items reverse-scored)	18 (worst)–126 (best)
	PSS	10-item self-report scale	0 (best) to 40 (worst); 0–13 = low, 14–26 = moderate, 27–40 = high stress
	PEI	6-item self-report	0 (worst) to 12 (best)
	ROS	1-item self-report scale	Satisfied (3 or 2), mostly satisfied (1), or dissatisfied (0, −1, −2, or −3)
	RM	3-item self-report scale	0 (worst) to 10 (best); raw data presented
	TAS	3-item self-report scale (pre-injury, current, future)	1 (low activity)–10 (very high activity)
Physical testing	SH^a^	Number of completed hops	Change in the injured leg
	Hop test battery	SLHD-3 repetitions or until improvement <10cm; distance hopped (cm)	Change in the injured leg, change in the uninjured leg, LSI
		SH-number completed hops in 30 s	
	POEs	SLMS-5 repetitions; POEs assessed throughout the entire movement	Total POEs score
		SD-5 repetitions; POEs assessed on loading leg throughout entire movement until both feet are on the floor	
		FL-3 repetitions; POEs assessed on the front leg from landing until maximum flexion of the knee	

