#### Adaptive design modification criteria

The mean scores of the main outcomes (side hop and ACL-RSI) will be compared in exploratory interim analyses once *n*=25 participants have been included in both groups. Analyses will be performed by a blinded third-party data management committee (DMC) and blinded to treatment arms until after an initial data analysis and interpretation. The purpose of the interim analysis is primarily to gain data with which a more reliable sample size can be calculated based on observed differences, as well as to identify potential benefits and harms which may thereby determine whether modifications are required. Therefore, differences in the main outcomes from baseline to 12 weeks will be compared using estimations from the previously defined clinically relevant differences as modification criteria, as both groups are expected to improve. Continuation without modification will be allowed if the between-groups difference in ACL-RSI is ≥5 points, and/or muscle function (LSI) in the side-hop test is ≥8 in favor of the MOTIFS group, each analyzed separately. These estimates correspond to a small to medium effect size (Cohen’s *d*≈0.1–0.3) based on previously defined clinically relevant values and will be used to determine the potential for the MOTIFS model to exhibit an effect. However, as previous studies which provide enough data for reliable calculation are lacking, these effect sizes are theoretical estimations which require further data to confirm. The estimates take into account the small sample size in the interim analysis and serve as a guide to whether the differences exhibit a trend indicating acceptable power upon completion of data collection, without unnecessarily prematurely ending the trial. If these initial criteria are not met, difference in enjoyment (PACES) scores of approximately 5 points will be deemed acceptable, estimated based on studies examining the effect of enjoyment on physical activity adherence in uninjured people [53]. Increased adherence to rehabilitation training will likely lead to improved rehabilitation outcomes based on a dose-response relationship, so increased enjoyment is considered an acceptable criterion for the continuation of the trial. Upon completing the interim analysis, the DMC will determine whether these criteria are met, and/or whether modifications are necessary, and a new sample size calculation will be performed.

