Due to the low range and number of items of the perceived stress scale, Patient Enablement Instrument, and Tegner Activity Scale, as well as the fact that both groups are expected to improve, chi-squared tests will be used to compare within-subjects between-groups means. Rehabilitation motivation and outcome satisfaction will be presented as raw data due to the low number of items. Attrition analyses will also be performed.

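### The planned non-parametric fallback, Wilcoxon signed-rank, is a paired test and cannot compare two independent arms; the chi-squared tests of means are a lesser error of the same kind

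*Protocol article*

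**What the plan says.** The Data analysis section of the protocol article names independent-samples t tests "to examine between-group differences of the change from baseline to a 12-week follow-up". The next sentence supplies the alternative, to be applied where appropriate: "equivalent non-parametric Wilcoxon signed-rank testing will be used to compare between-group differences". That sentence does not say what triggers the switch. The only check in the section that could do so is the normality check: "All outcome variables will be examined for normality using appropriate testing (e.g., Kolmogorov-Smirnov"). It covers every outcome, so it includes both main outcomes, ACL-RSI and side-hop change.

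The same section treats three secondary scales differently. "Due to the low range and number of items of the perceived stress scale, Patient Enablement Instrument, and Tegner Activity Scale", and because both groups should improve, it says that "chi-squared tests will be used to compare within-subjects between-groups means".

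The arms are independent. Under Participants and randomization, "participating clinics are block randomized by a third party", and no matching of participants between arms is described anywhere. The rank-sum (Mann-Whitney) test is not named in the article.

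**The concern.** The signed-rank test takes one set of differences and asks whether they are centred on zero. It needs one sample or true pairs. The non-parametric counterpart of an independent-samples t test is the rank-sum test, so the sentence names a test that cannot do what the sentence asks of it.

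The fallback is open to both main outcomes. The natural input for a signed-rank test here is each participant's change score, and the test then detects improvement over time. The protocol expects that improvement whatever the treatment does: "as both groups are expected to improve" (Adaptive design modification criteria). A significant result would therefore carry no information about MOTIFS against care-as-usual.

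The chi-squared wording has a related fault. A chi-squared test compares category frequencies. It does not compare means, and it takes no account of the order of the categories. The article does not say what would be tabulated. This part concerns only secondary outcomes, which the section itself gives less weight.

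**Working it through.** **Inputs from the protocol.** Total sample 106, allocation 1:1, drop-out 20%, significance at p<0.025 (sidedness not stated; two-sided assumed here). Per arm: 106/2 = 53 enrolled; 53 × 0.80 = 42.4, so about 42 evaluable. The plan gives no operating figure for the fallback, so there is nothing to reproduce on this point. The effect size, SD and ICC behind 106 are not given, so 106 cannot be re-derived either; the point does not depend on it.

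**Assumed inputs.** Change scores are normal with SD 1. Both arms improve by the same 0.3, 0.5 or 0.8 SD, so there is no treatment difference. Each setting has 4,000 simulated trials.

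**Step 1: signed-rank on change scores.** A valid between-arm test should reject in about 2.5% of runs.

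| Per arm | Improvement in both arms | t test | Rank-sum | Signed-rank, one arm | Signed-rank, both arms pooled |
|---|---|---|---|---|---|
| 42 | 0.3 SD | 2.1% | 2.0% | 33% | 66% |
| 42 | 0.5 SD | 2.1% | 2.1% | 79% | 98.5% |
| 42 | 0.8 SD | 2.5% | 2.3% | 99.7% | 100% |
| 53 | 0.3 SD | 2.2% | 2.4% | 42% | 77% |
| 53 | 0.5 SD | 2.7% | 2.6% | 89% | 99.8% |
| 53 | 0.8 SD | 2.0% | 1.7% | nearly 100% | 100% |

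The simulation error on a 2.5% rate is √(0.025 × 0.975/4000) ≈ 0.25 percentage points, so the t and rank-sum columns agree with the nominal level to within about three such errors. The signed-rank columns follow the assumed improvement, because improvement is what that test measures.

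**Step 2: pairing people across arms.** The other literal use is to pair each MOTIFS participant with a care-as-usual participant. No basis for pairing exists, so the result depends on an arbitrary choice. In one simulated data set with 42 per arm, 5,000 random pairings gave p from 0.03 to 0.60, while rank-sum gave a single p of 0.20.

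**Step 3: chi-squared on an ordered score.** Assumed: an integer 0–12 scale (the PEI range in Table 3), 42 per arm, two-sided alpha 0.025, 3,000 runs, each score value treated as a category.

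| Situation | Chi-squared | Rank-sum | t test |
|---|---|---|---|
| Means 7.5 and 6, SD 2.5 (shift 1.5/2.5 = 0.6 SD) | 14% | 64% | 67% |
| Means both 6, SD 1.2 and 3.2 | 77% | 3.5% | 2.6% |

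Chi-squared misses most of a real shift in means and reacts strongly when the means are equal but the spread differs. It is not a test of means.

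**Step 4: the reason given for chi-squared.** Table 3 lists the PSS as 10 items scored 0–40. ACL-RSI has 12 items and receives a t test. A low range and few items therefore do not describe the PSS. They fit the PEI (6 items, 0–12) and TAS (3 items, 1–10) better, but they argue for a rank or ordinal method, which keeps the order of the scores.

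**The case against.** The strongest reply is that this is a naming slip. The sentence calls its test the equivalent of the independent-samples t test and states a between-group purpose, and the final analysis goes to a third-party statistician (Data management), who would probably use rank-sum. The fallback is also conditional; the primary t test is correctly named for two independent groups. All of that stands, and it limits the consequence. It does not make the named test usable. An analyst who notices has to choose another test without a pre-specified name for it.

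Three stronger readings are tempting, and the documents do not support them.

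- A reader might infer that the trial would falsely claim a treatment effect at the signed-rank rates in the table. The protocol nowhere says that a within-arm or pooled test will be used to claim one. The rates show what the named test measures; they are not the error rate of the stated plan.
- A reader might infer that chi-squared on the PSS means a very sparse table of raw scores. Table 3 gives three bands, "0–13 = low, 14–26 = moderate, 27–40 = high stress". With 106 × 0.80 ≈ 85 evaluable people and 3 × 2 = 6 cells, the average is 85/6 ≈ 14 per cell, although a rarely used band could still be thin. A banded test could be valid, but it would compare proportions and not means or change. The PEI and TAS have no bands.
- A reader might infer that the chi-squared analysis throws baseline away. The article's wording refers to within-subject comparison, which may mean a categorised change. The supportable criticism is that the tabulated quantity is undefined.

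**Conclusion.** Wrong as written, and worth correcting before the final analysis. The signed-rank part is the more important because the fallback can reach both main outcomes. It is probably a slip for rank-sum. If it were followed literally on change scores, the rejection rate with no treatment difference would be about 33% to nearly 100% within one arm, against about 2% for rank-sum. That range rests on normal change scores, equal improvement of 0.3 to 0.8 SD in both arms, 42 per arm and two-sided alpha 0.025. The protocol supplies no SD of change and no indication of how likely the fallback is to be used.

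The chi-squared part is secondary. The test does not compare means, the reason given does not fit the PSS, and three lower-weight outcomes are affected.

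**What to change.** In Data analysis, replace *Wilcoxon signed-rank* with *Wilcoxon rank-sum (Mann-Whitney) test on change from baseline to 12 weeks*.

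Replace the chi-squared sentence. Analyse PSS change with the same between-group test as the other scores. Analyse PEI and TAS with rank-sum, on change where a baseline is measured, or with ordinal regression. Drop the low-range justification for the PSS. If a banded PSS comparison is still wanted, present it as a comparison of proportions alongside the score analysis.

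The cost is two sentences of analysis text. Data collection and visits do not change, and the recruitment target is not affected. If a statistical analysis plan exists, it should carry the same wording. Rank-sum, like the t test, takes no account of randomization by clinic; that is a separate issue which this correction does not settle.
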